#### **9.5 Recording of AEs and SAEs**

When an AE/SAE occurs, it is the responsibility of the investigator to review all documentation (e.g. hospital progress notes, laboratory, and diagnostic reports) relative to the event. The investigator will then record all relevant information regarding an AE/SAE in to the CRF.

For each adverse event, start and stop dates, action taken, outcome, intensity (see Section 9.8.1) and relationship to study product (causality) (see Section 9.8.2) must be documented. If an AE changes in frequency or intensity during a study, a new entry of the event must be made in the CRF.

The investigator will attempt to establish a diagnosis of the event based on signs, symptoms, and/or other clinical information. In the absence of a diagnosis, the individual signs/symptoms should be documented.

All details of any treatments initiated due to the adverse event should be recorded in the subject’s notes and the CRF.

#### **9.6 Prompt Reporting of SAEs to the Study Management Centre**

Once an investigator becomes aware that an SAE has occurred in a study subject, he/she will immediately notify the Study Management Centre (Melbourne Brain Centre, Royal Melbourne Hospital, University of Melbourne) by contacting the study monitor via telephone to notify him/her of the event. The SAE form must be completed as thoroughly as possible with all available details of the event, signed by the investigator (or appropriately qualified designee), and faxed to the study monitor within 24 hours of first becoming aware of the event.

Protocol Number: UOM2102

Protocol Title: ETERNAL LVO

If the investigator does not have all information regarding an SAE, ***he/she will not wait to receive additional information before notifying the study monitor*** of the event and completing the form. The form will be updated when additional information is received.

The investigator will always provide an assessment of causality at the time of the initial report as described in Section 9.8.2, “Assessment of Causality”. If data obtained after reporting indicates that the assessment of causality is incorrect, then the SAE form may be appropriately amended, signed and dated, and resubmitted to the Study Management Centre.

In accordance with local IEC requirements, the investigator must also notify their Ethics Committee of any SAEs according the guidelines of the Ethics Committee.

The investigator, and others responsible for subject care, should institute any supplementary investigations of serious adverse events based on their clinical judgement of the likely causative factors. This may include seeking further opinion from a specialist in the field of the adverse event.

## 9.7 Expeditable Events

Expeditable events are those adverse events that are **CAUSALLY** related to the study product, **AND** that are both **SERIOUS** (see Section 9.2) and **UNEXPECTED** (see Section 9.8.3). Such events are subject to expedited reporting to regulatory authorities and will be reported within the stipulated timelines.

## 9.8 Evaluating AEs and SAEs

### 9.8.1 Assessment of Intensity

The investigator will make an assessment of intensity for each AE and SAE reported during the study. The assessment will be based on the investigator’s clinical judgement. The intensity of each AE and SAE recorded in the CRF should be assigned to one of the following categories:

**Mild:** An event that is easily tolerated by the subject, causing minimal discomfort and not interfering with everyday activities.

**Moderate:** An event that is sufficiently discomforting to interfere with normal everyday activities.

**Severe:** An event which is incapacitating and prevents normal everyday activities.

An AE that is assessed as severe should not be confused with an SAE. Severity is a category utilised for rating the intensity of an event; and both AEs and SAEs can be assessed as severe. An event is defined as “serious” when it meets one of the pre-defined outcomes as described in Section 9.2 “Definition of an SAE”.

### 9.8.2 Assessment of Causality

The investigator is obligated to assess the relationship between investigational product and the occurrence of each AE/SAE. The investigator will use clinical judgment to determine the relationship. Alternative causes, such as natural history of the underlying diseases, concomitant therapy, other risk factors, and the temporal relationship of the event to the investigational product will be considered and investigated. The investigator will also consult the CIB and/or product information in the determination of his/her assessment.

The causal relationship to the study product assessed by the Investigator (or medically qualified delegate) should be assessed using the following classifications:

- |                    |                                                                                                                                                                                                                                                                 |
|--------------------|-----------------------------------------------------------------------------------------------------------------------------------------------------------------------------------------------------------------------------------------------------------------|
| Not Related | In the Investigator's opinion, there is not a causal relationship between the study product and the adverse event.                                                                                                                                              |
| Unlikely    | The temporal association between the adverse event and study product is such that the study product is not likely to have any reasonable association with the adverse event.                                                                                    |
| Possible    | The adverse event could have been caused by the study subject's clinical state or the study product.                                                                                                                                                            |
| Probable    | The adverse event follows a reasonable temporal sequence from the time of study product administration, abates upon discontinuation of the study product and cannot be reasonably explained by the known characteristics of the study subject's clinical state. |
| Definitely  | The adverse event follows a reasonable temporal sequence from the time of study product administration or reappears when study product is reintroduced.                                                                                                         |

There may be situations when an SAE has occurred and the investigator has minimal information to include in the initial report to the DSMC. However, it is very important that the investigator always makes an assessment of causality for every event prior to transmission of the SAE form the DSMC. The investigator may change his/her opinion of causality in light of follow-up information, amending the SAE form accordingly. The causality assessment is one of the criteria used when determining regulatory reporting requirements.

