## 7.2 Study Procedures

### 7.2.1 Day 0 – Treatment

**Intravenous thrombolytic treatment:** Patients will receive open-label intravenous tenecteplase at a dose of 0.25 mg/kg, given as a bolus or ‘standard of care’, which will include intravenous alteplase at the standard dose of 0.9 mg/kg up to a maximum of 90mg (10% as bolus and the remainder over 1 hour), or no thrombolytic. Randomisation will be performed as described above. The time of bolus and infusion commencement will be recorded.

Close neurological observation will be conducted primarily during the first 48 hours after treatment administration according to local clinical practice.

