## **8.3 Administration**

After reconstitution of the investigational product, a dedicated IV cannula should be used for administration. The dose of tenecteplase to be administered is given as a bolus over approximately 5 seconds. The investigational product should be used immediately after reconstitution. No other anticoagulants or antiplatelet agents are to be given within 24 hours of administration of the investigational product.

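### In section 9.8.2 the causality level 'Definitely' is easier to meet than 'Probable', and the criteria do not fit a single tenecteplase bolus, so AE/SAE attribution is liable to be misclassified

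*Protocol*

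**What the plan says.** Protocol section 9.8.2 obliges the investigator to rate the relation of every AE and SAE to the study product on five levels: Not Related, Unlikely, Possible, Probable, Definitely. The three upper levels are defined as follows.

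- *Possible*: "The adverse event could have been caused by the study subject's clinical state or the study product".
- *Probable*: reasonable timing after administration, and in addition the event "abates upon discontinuation of the study product and cannot be reasonably explained by the known characteristics of the study subject's clinical state". All three conditions must hold together.
- *Definitely*, the top level, offers two alternatives: "The adverse event follows a reasonable temporal sequence from the time of study product administration or reappears when study product is reintroduced".

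Above the scale, the same section asks for clinical judgment. It lists what is to be considered and investigated: "Alternative causes, such as natural history of the underlying diseases, concomitant therapy, other risk factors, and the temporal relationship of the event".

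On the products, section 8.3 states: "The dose of tenecteplase to be administered is given as a bolus over approximately 5 seconds". Section 7.2.1 gives alteplase, one option in the control arm, as "10% as bolus and the remainder over 1 hour".

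On use of the rating, section 9.6 requires it in the initial SAE report, and section 9.8.2 says that it is among the inputs to regulatory reporting. Section 9.7 makes an event expeditable when it is causally related, serious and unexpected: "Such events are subject to expedited reporting to regulatory authorities and will be reported within the stipulated timelines".

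**The concern.** A causality scale should become harder to satisfy as certainty rises. Here the top two levels run the other way. The conditions of 'Probable' are joined by 'and', while the two limbs of 'Definitely' are joined by 'or'. The test on alternative explanations appears in 'Probable' and is absent from 'Definitely'.

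The levels also fail to separate the typical early event in acute stroke, one that follows the drug in time and could equally come from the infarct. Such an event meets 'Possible' and 'Definitely' at once, and the definitions give no rule for choosing between them.

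At stake is the meaning of a mandatory safety rating collected at 50 to 75 centres (section 6) in an open-label trial (section 8.5). If some investigators apply the definitions literally and others override them, the same event will receive different ratings at different sites.

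**Working it through.** The protocol gives no figure to reproduce. The check is whether the definitions are ordered and whether they can be applied to the product.

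**Inputs**, all from 9.8.2. Each is coded 1 if true and 0 if not:

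- T: reasonable timing after administration
- A: abates when the product is stopped
- U: not reasonably explained by the patient's clinical state
- R: returns when the product is given again

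**Rules as written**

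- Probable = T and A and U
- Definitely = T or R

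**Step 1: all patterns.** Four yes/no items give 2 × 2 × 2 × 2 = 16 patterns.

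- Probable needs T = A = U = 1 with R free, which gives 2 patterns.
- Definitely is met by all 8 patterns with T = 1, and by the 4 with T = 0 and R = 1, which gives 8 + 4 = 12 patterns.
- Patterns meeting Probable but not Definitely: 0, because Probable requires T = 1 and T = 1 already satisfies Definitely.

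The upper level is therefore strictly easier to meet than the one below it.

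**Step 2: single bolus.** With a bolus lasting about 5 seconds (8.3) there is nothing to stop once an event appears, and no second administration is planned, so A = 0 and R = 0. Four patterns remain.

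| T | U | Probable (T and A and U) | Definitely (T or R) |
|---|---|---|---|
| 0 | 0 | no | no |
| 0 | 1 | no | no |
| 1 | 0 | no | yes |
| 1 | 1 | no | yes |

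Probable is met by 0 of 4 and Definitely by 2 of 4. Those two are all the events with reasonable timing, including the row with U = 0, where the clinical state explains the event.

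**Step 3: overlap with Possible.** An event in the row T = 1, U = 0 could have come from the clinical state or from the product. It fits the wording of Possible and also that of Definitely.

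**Step 4: difference between arms.** Part of the alteplase dose runs over 1 hour (7.2.1) and can in principle be stopped, so A = 1 is possible there. If investigators take 'study product' to include alteplase, Probable can be reached in some control patients and never in the tenecteplase arm.

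**Step 5: effect of a repair.** With A and R removed and Probable = T and U, one of the four bolus patterns qualifies (T = 1, U = 1). If Definitely must include T and U plus a further condition, every Definitely event also meets Probable, and the row with U = 0 no longer reaches either level.

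The pattern counts describe the logic of the wording. They are not frequencies of events.

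**The case against.** The best defence is that 9.8.2 makes causality a judgment and not an algorithm. Investigators must consider and investigate other causes and consult the product information. 'Possible' remains open for events that the stroke could explain, and 'Not Related' rests on the investigator's opinion. A sensible investigator would not rate infarct swelling as definitely drug-related.

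This defence stands in part. A reader might infer that early events *will* be rated 'Definitely'. The document does not support that; it supports only that ratings are *liable* to be wrong. The defence does not remove the defect. The same section directs that the relation be rated with the listed classifications, and the general instruction pulls against the definition of the top level. That conflict is itself a source of inconsistency.

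Three other strong readings are tempting and are not supported.

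- **That safety conclusions are distorted.** In section 12.2, sICH is defined by PH2 with an NIHSS increase, death is from any cause, and mRS 5-6 is a score. The Haybittle-Peto monitoring in 12.4 compares deaths and sICH between arms. None of these uses attribution.
- **That expedited reporting is wrong by a known amount.** Section 9.7 sets no cut-off on the five levels, and an event must also be serious and unexpected. If 'Possible' and above were treated as related, confusion among the top three levels would change no report. Only a move up from 'Not Related' or 'Unlikely' would.
- **That the scale of misrating can be read from the planned 370 patients per arm (maximum 500), or from the background statement that more than 50% of large-vessel-occlusion patients are dead or highly disabled at 3 months.** Neither figure counts misrated events.

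**Conclusion.** The defect is present on the face of 9.8.2. 'Definitely' is a weaker test than 'Probable' and overlaps 'Possible', and the discontinuation and reintroduction criteria cannot apply to tenecteplase as given in 8.3. Followed literally, the scale gives wrong ratings; applied with judgment, it gives ratings that need not mean the same thing across sites.

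The consequence is confined to AE/SAE attribution and, through it, to the causality criterion in 9.7. The size of the reporting effect cannot be determined from the document. The efficacy analysis, the three listed safety outcomes and the DSMC boundaries are unaffected.

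The conclusion assumes that 'or' in the top definition carries its ordinary meaning and that each tenecteplase patient receives one bolus.

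**What to change.** Reword the top two levels of 9.8.2 so that stringency rises. 'Definitely' should require at least everything that 'Probable' requires, including the absence of a reasonable alternative explanation. What further evidence separates the two is for the sponsor to define. Remove the discontinuation and reintroduction criteria, or replace them with criteria usable for a single bolus. Bring the SAE form into line with the new wording.

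The cost is a short protocol amendment, a revised form and a note to sites. Events already reported may need to be re-rated. No analysis or sample size changes.

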### 9.8.3 Assessment of Expectedness

**Expected** An adverse reaction, the nature or severity of which is consistent with the applicable product information (e.g. Investigator's Brochure for an unapproved medicinal product).

**Unexpected** An adverse reaction, the nature or severity of which is not consistent with information in the relevant source document (e.g. Investigator's Brochure for an unapproved medicinal product).

Protocol Number: UOM2102

Protocol Title: ETERNAL LVO

## **9.9 Follow-up of AEs and SAEs**

After the initial AE/SAE report, the investigator is required to proactively follow each subject and provide further information to the DSMC on the subject's condition.

All AEs and SAEs documented at a previous visit/contact and are designated as ongoing, will be reviewed at subsequent visits/contacts.

All AEs and SAEs will be followed until resolution, until the condition stabilises, until the event is otherwise explained, or until the subject is lost to follow-up. Once resolved, the appropriate AE/SAE CRF page(s) will be updated. The investigator will ensure that follow-up includes any supplemental investigations as may be indicated to elucidate the nature and/or causality of the AE or SAE. This may include additional laboratory tests or investigations, histopathological examinations, or consultation with other health care professionals.

New or updated information will be recorded on the originally completed SAE form, with all changes signed and dated by the investigator. The updated SAE form should be resent to the Study Management Centre.

## **9.10 Post-study AEs and SAEs**

A post-study AE/SAE is defined as any event that occurs outside the AE/SAE detection period as defined in Section 9.4 "Time Period, Frequency, and Method of Detecting AEs and SAEs" of the protocol.

Investigators are not obligated to actively seek AEs or SAEs in former study participants. However, if the investigator learns of any SAE, including death, at any time after a subject has been discharged from the study, and he/she considers the event reasonably related to the investigational product, the investigator will promptly notify the DSMC.

# **10. Subject completion and discontinuation**

## **10.1 Subject Completion**

Subjects will have completed their involvement with the study when the follow up visit has occurred at 90 days, data has been entered into the CRF, and any queries or inconsistencies relating to the data have been resolved with the investigator.

## **10.2 Subject Withdrawal**

Subjects who elect to withdraw from the study should attend a final withdrawal visit. The date and reason for patient withdrawal should be recorded on the 'Study End' page of the CRF.

### **10.3 Discontinuation Criteria**

The study may be terminated prematurely by the principal investigator or his/her designee and the sponsor. Reasons include but are not limited to:

- The number and/or severity of adverse events justify discontinuation of the study
- New data become available which raise concern about the safety of the investigational product, so that continuation might cause unacceptable risks to subjects.

In addition the Sponsor reserves the right to discontinue the trial prior to inclusion of the intended number of subjects, but intends only to exercise this right for valid scientific or administrative reasons.

After such a decision, the Investigator must contact all participating subjects within two weeks, and written notification must be sent to the Ethics Committee.

## **11. Case report form**

A Case Report Form (CRF) will be completed for each study subject summarising all clinical screening and study data. Subjects will only be referred to in the CRF by their subject number and initials in order to retain subject confidentiality. The completed original CRFs are to be sent to the Sponsor as soon as practical after completion and review. A copy of each completed CRF is to be retained by the Investigator for a period of time as determined by local regulations. The identification of data to be recorded directly in to the CRF (i.e. no prior written or electronic record of data), and to be considered to be source data, is outlined in the Source Document Designation Form.

## **12. Data analysis and statistical considerations**

### **12.1 Objective**

The primary objective of the study is to test the hypothesis that the thrombolytic tenecteplase (TNK) is superior to current best practice (alteplase 0.9mg/kg or no lysis) in achieving excellent functional outcome or return to the premorbid Modified Rankin Scale in acute ischemic stroke patients presenting with an ischemic stroke due to a large vessel occlusion and who have a significant volume penumbral tissue on multimodal CT or MRI, within 24 hours after symptom onset.

### **12.2 Endpoints**

#### **Primary Outcome**

- The proportion of patients with Modified Rankin Scale (mRS) 0-1 (no disability) or return to baseline mRS (if baseline premorbid mRS =2) at 3 months.

## Secondary Outcomes

### Efficacy

- Proportion of patients achieving early clinical improvement (reduction in acute – 24 hour NIHSS score of  $\geq 8$  or 24 hour NIHSS 0-1).
- Proportion of patients with Modified Rankin Scale 0-2 at 3 months
- Ordinal analysis of mRS at 3 months
- Proportion of patients with TICI 2b/3 on initial DSA run prior to thrombectomy

